
#### Non-EEG/ERP-derived pharmacodynamic data

##### Pain intensity and unpleasantness ratings

Participants will be asked to rate the intensity of the sensation elicited by each laser and pinprick stimuli delivered to obtain the above-described EEG biomarkers, using a 101-point pain rating scale where 0 is defined as “no pain at all” and 100 is defined as “most intense pain imaginable” (detailed in a separate operational manual). These ratings, obtained after each stimulus, will allow changes in EEG biomarker measures to be related to changes in perception. Medication, induction of hyperalgesia, and/or effects of the medication on hyperalgesia may affect the intensity of the percept elicited by the different stimuli.

Furthermore, at the end of each laser and pinprick stimulation blocks, the participants will be asked to rate the average unpleasantness of the preceding series of stimuli that were delivered in that block using a 101-point unpleasantness rating scale where 0 is defined as “not unpleasant at all” and 100 is defined as “extremely unpleasant.”

Average pain ratings and unpleasantness ratings obtained at each PD assessment time-point and the results of the hyperalgesia testing will be calculated and entered in the source paper documentation before entering in the electronic CRF. Furthermore, all individual pain ratings obtained after each stimulus, all unpleasantness ratings obtained after each stimulation block, and the results of the hyperalgesia testing will be sent and stored centrally at UCLouvain, along with the pharmacodynamic data.

##### Patient-reported outcome measures (PROMs)

During the screening visit, participants will be asked to complete a set of PROMs assessing their psychological traits. During each study period, participants will be asked to complete an additional set of PROMs assessing their expectations, tiredness, and anxiety.

The following PROMs will be completed during the screening visit, in the following order:
*Self-assessment of general health using the PROMIS Global-10 questionnaire.* The PROMIS Global-10 is a publicly available global health assessment tool that allows measurements of symptoms, functioning, and healthcare-related quality of life for a wide variety of chronic diseases and conditions. It consists of 10 items that assess general domains of health and functioning including overall physical health, mental health, social health, pain, fatigue, and overall perceived quality of life.*Self-assessment of self-efficacy using 3 items of the General Self-Efficacy Scale (GSE)*, followed by a short break. The GSE [38] is a psychometric scale that is designed to assess optimistic self-beliefs to cope with a variety of difficult demands in life.*Self-assessment of trait anxiety using the General Anxiety Disorder-7 questionnaire (GAD-7)*. The GAD-7 is a brief scale on anxiety. This easy-to-use self-administered patient questionnaire is used as a screening tool and severity measure for generalized anxiety disorder.*Self-assessment of depression using the Patient Health Questionnaire-9 (PHQ-9)*, followed by a short break. The Patient Health Questionnaire (PHQ) is a diagnostic tool for mental health disorders used by health care professionals that is quick and easy to complete. The PHQ-9 is a tool specific to depression and simply scores each of the 9 criteria based on the mood module from the original PRIME-MD, a diagnostic tool containing modules on 12 different mental health disorders.*Self-assessment of pain catastrophizing using the Pain Catastrophizing Scale (PCS)* [39], followed by a short break. The PCS is a 13-item scale, with each item rated on a 5-point scale: 0 (not at all) to 4 (all the time). The PCS is broken into three subscales being magnification, rumination, and helplessness. The scale was developed as a self-report measurement tool that provides a valid index of catastrophizing in clinical and non-clinical populations. The results of the initial development and validation studies indicate that the PCS is a reliable and valid measurement tool for catastrophizing.*Self-assessment of pain sensitivity using the Pain Sensitivity Questionnaire (PSQ))* [40]. The questionnaire contains a series of 17 questions in which the subject is asked to imagine himself in certain situations. He should then decide if these situations would be painful and how painful they would be. The PSQ uses a numeric rating scale from 0 = not at all painful to 10 = most severe pain imaginable.

The following PROMs assessing subject expectations will be completed at the beginning of each study period:
*Anxiety* will be assessed by asking participants: “On a scale of 0–100, please rate, how anxious you are about the upcoming experiment, with 0 being ‘not anxious at all’ and 100 being ‘extremely anxious’.”*Pain expectation* will be assessed by asking participants: “On a scale of 0–100, please rate how much pain do you anticipate experiencing during the upcoming experiment, with 0 being ‘no pain at all’ and 100 being ‘pain as bad as you can imagine’.”*Expectation of IMP-induced pain relief* will be assessed by asking participants: “On a scale of 0–100, please rate how much pain relief you expect from the medication, with 0 being ‘expecting no relief’ and 100 being ‘expecting complete relief’.”

The following PROMs assessing tiredness and anxiety will be assessed 5 h after IMP administration:
*Self-assessment of tiredness*. The subject will be asked: “On a scale of 0–100, please rate, how alert or sleepy you feel right now, with 0 being ‘very alert’ and 100 being ‘very sleepy’.”*Self-assessment of state anxiety using the State and Trait Anxiety Inventory (STAI-Y).* The State-Trait Anxiety Inventory (STAI, by Mind Garden, Inc.©) is a psychological inventory based on a 4-point Likert scale and consists of 2 × 20 questions on a self-report basis [41]. The STAI-Y measures two types of anxiety state anxiety, or anxiety about an event, and trait anxiety (20 items), and anxiety level as a personal trait characteristic (20 items). Only state anxiety will be measured using this questionnaire. Higher scores are positively correlated with higher levels of anxiety. Its most current revision is Form Y. It is used in diagnoses, in clinical and other medical settings, as well as in research and is differentiating between anxiety and depression.

The PROMs will be collected via questionnaires in the local language. Scores calculated from these questionnaires will be entered in the source paper documentation before entering into the electronic CRF as described above. The subjects will be instructed on how to fill out the questionnaires. No queries will be issued to the investigator for these data, except for clarification of subject identifiers and any operational issues. All PROMs reported on paper will stay as source data at the trial site. The investigator will be responsible for the accurate transfer of these data into the electronic CRFs.

#### Hyperalgesia testing

The intensity of the sensation elicited by calibrated mechanical pinprick stimuli will be assessed at the left (HFS-sensitized) and right (non-sensitized) forearms. At the sensitized forearm, the extent of the area of secondary hyperalgesia will be measured by locating the position at which participants report a change in the intensity of the sensation elicited by mechanical pinprick stimuli delivered along 8 radial directions relative to where HFS was applied on the skin (proximal, proximal-lateral, lateral, lateral-distal, distal, distal-medial, medial, and medial-proximal directions). The same approach will be used to assess the intensity and area of dynamic allodynia (if present), using a standardized brush to deliver dynamic tactile stimuli. These assessments will allow the perceptual changes observed in IMI2-PainCare-BioPain-RCT3 to be compared to those observed in the other three RCTs of the BioPain subtopic of the PainCare project (IMI2-PainCare-BioPain-RCT1, 2, and 4).

### Plans to promote participant retention and complete follow-up {18b}

To promote participant retention, at the screening visit and at the four study periods, some exclusion criteria have been defined as temporary exclusion criteria, such as transient illness, changes in physical exercise, and medications taken in the past 2 weeks.

If at screening one or more of these temporary exclusion criteria are met, the subject can be included in the study. In this case, before the start of the first study period, the met temporary exclusion criteria of the screening visit will be checked again, and their absence will be verified before the first study period takes place.

Similarly, if screening of exclusion criteria for eligibility during a study period shows that one or more temporary exclusion criteria are met, the start of the study period may be postponed and re-scheduled. In this case, the previously met temporary exclusion criteria of the study period will be checked again and their absence will be verified before the subject is eligible for the period.

### Data management {19}

Data management will be performed by the Interdisciplinary Center for Scientific Computing at University Heidelberg. Documentation of the responsibilities and delegation thereof will be maintained in the trial master file.

All aspects of the data management process (including data validation and query management, medical coding, ECG data, biomarker data) and data lock procedures are described below and detailed in the data management plan.

#### Source data

All source data arising from the trial will be kept by the investigator, who will provide direct access for trial-related monitoring, audits, ethics committee review, and regulatory inspection.

#### Case report forms

Case report forms for each subject will be provided to the investigator in electronic format and will serve to create the local source documentation in paper format. The investigator and personnel delegated the task will use these paper-form documents to record the source data information required by the protocol. The source data documentation will be entered into a validated electronic CRF system via a secured access to the Heidelberg University computing center. The collected data will reside on secure servers of the Heidelberg University. Entry, corrections, and alterations of data within the system can only be performed by the investigator or other authorized personnel under their supervision and will be captured by the system’s audit trail. Entries will be checked against appropriate source documents by authorized CRAs as deemed appropriate in the monitoring guidelines. Dedicated users (e.g., the investigator, designated persons at the trial site, authorized sponsor representatives, and from other parties involved, e.g., data management) will be trained and receive access rights according to their role in the trial. All users will have access to the system and be able to review their data on an ongoing basis. After completion of the subject’s CRF, the CRF will be signed electronically by the investigator. With the investigators signature, it is confirmed that the data in the CRF are checked, complete, accurate, and in alignment with the source data. Changes to the CRF after initial signing by the investigator will need re-signing. With database lock, the edit rights to the CRFs will be removed, but the investigator will retain access to view the CRFs. The nature and location of all source data/clinical documentation will be identified and documented by the investigator to ensure that all sources of original data required to complete the CRF are known to the sponsor and/or trial site personnel and are accessible for verification during trial-related monitoring, audits, relevant IEC review, and inspection(s). During trial conduct, the Interdisciplinary Center for Scientific Computing at University Heidelberg is responsible for data security related to the data captured in the CRF.

#### Pharmacodynamic data

Copies of the raw pharmacodynamic source data will be electronically transferred to UCLouvain. The data will be stored on secured servers, which have backup onto a second server located in a physically distinct room, also using a secured storage protocol. Signal processing of the raw data to extract the parameters of interest will also be done centrally at UCLouvain using the Letswave 6 matlab toolbox for the analysis of EEG data (http://letswave.org; UCLouvain; hosted on the Github repository). All primary, secondary, and exploratory EEG biomarker endpoints derived from these analyses, as well as the non-EEG biomarker endpoints will be transferred to the relational database hosted at the Heidelberg University computing center. The obtained endpoint parameters will be entered by UCLouvain into a relational database located at the Heidelberg University computing center.

#### Pharmacokinetic data

Pharmacokinetic concentrations and pharmacokinetic parameters measured by ESTEVE will be uploaded by ESTEVE to the relational database at the Heidelberg University computing center.

#### Investigator’s site file and the trial master file

At each site, the Principal Investigator will be responsible for the filing of all essential documents in an investigator’s site file. The sponsor will be responsible for the timely filing of all essential documents in the trial master file. As applicable, these files must be available at monitoring visits and during audits or regulatory inspections. After trial completion, the Principal Investigator will ensure that all source data/documentation related to the trial is recorded, handled, and stored in a way that allows its accurate reporting, interpretation, and verification. The Principal Investigator will take measures to prevent accidental or premature destruction of these documents.

The Principal Investigator will keep the investigator’s site file, the source data/documentation arising from the trial according to the prescribed record retention period in the country and/or according to the hospital policy.

### Confidentiality {27}

Subject trial data will be stored in a manner maintaining confidentiality in accordance with applicable regulatory requirements.

The source data transferred from each site to UCLouvain for extraction of biomarker parameters, as well as the CRF data, will not contain any data that can identify the individual persons (such as name and social security number) except for a code, i.e., the data will be pseudoanonymized.

The investigator will ensure that any documents or data given to the sponsor or authorized sponsor representatives do not contain information that would affect the confidentiality of the subject’s identity.

All subject-related data will be obtained as described in this protocol document. There is no need to examine, analyze, verify, nor reproduce any healthcare or other records of the trial subjects.

### Plans for collection, laboratory evaluation, and storage of biological specimens for genetic or molecular analysis in this trial/future use {33}

#### Bioanalytical assays

The analysis of drug levels at all the different sampling times will be performed on pharmacokinetic samples collected from trial subjects who will be randomized to receive an active treatment (tapentadol, pregabalin, or lacosamide). Placebo samples will be analyzed at a single time-point around Tmax of drugs.

Drug concentrations of tapentadol, pregabalin, and lacosamide will be analyzed by ESTEVE Bioanalysis and ADME Development Department using a validated method under GLP (Good Laboratory Practice). The three drugs will be identified and quantified using HPLC method with tandem mass spectrometric detection (LC-MS/MS). Developed assays will be fully validated in terms of selectivity, linearity, accuracy, precision, recovery, matrix effects, and stability using official guideline on bioanalytical methods. Full details of the different analytical methods used will be described in the respective bioanalytical method validation report, and drug levels quantified in human plasma samples will be also reported in the respective bioanalytical report.

#### Bioanalytical laboratory unblinding

The bioanalytical laboratory will be unblinded in order to analyze multiple time-points from the specific active treatments and single time-points from corresponding placebos. The randomization list will be sent to the Bioanalysis and ADME Development Department at ESTEVE PHARMACEUTICALS, S.A. (ESTEVE) in order to analyze plasma drug levels of the active treatments (tapentadol, pregabalin, and lacosamide; multiple time-points) and placebo (single time-point). These analyses will be conducted when the clinical study is finished but the dataset is not yet locked. Therefore, the bioanalytical laboratory will recode the subject’s numbers to generate blinded results so that the investigator and the sponsor can review the results and remain blinded.

#### Calculation of pharmacokinetic parameters

The individual plasma concentration/time profiles for each analyte (tapentadol, pregabalin, and lacosamide) will be presented using the actual sampling times whereas the mean plasma concentration/time profiles will be presented using the theoretical sampling times. The plasma concentration data will be presented graphically for each analyte in a number of ways using both a linear and log-linear scale.

For each compound, relevant PK parameters will be calculated by standard non-compartmental methods for those subjects with sufficient plasma concentration data using Phoenix 64® WinNonLin® (Version 6.3 or later) with a log-linear terminal phase assumption. All reported sampling time deviations will be taken into consideration for evaluation of PK parameters.

For all three drugs, whenever applicable, the following standard non-compartmental pharmacokinetic parameters and drug-exposure-related metrics will be estimated in each subject, including:
*C*_max_: maximum plasma concentration.*t*_max_: time to reach maximum plasma concentration.λz: the terminal phase constant will be calculated by linear regression of the last phase of the curve (log concentration vs time).*t*_1/2_: terminal half-life will be determined with the expression *t*_1/2_ = 0.693/λz.AUC0-*t*: Area under the plasma concentration-time curve from time zero to last quantifiable concentration calculated by the linear and/or log trapezoidal rule.AUC0-*∞*: The area under the curve of plasma levels vs time from zero to infinite will be obtained with the expression AUC0-∞ = AUC0-*t* + Clast/λz, where Clast is the predicted plasma concentration at the last time measured.

A descriptive analysis will be provided for each derived PK parameter. Below limit of quantitation (BLQ) concentrations will be treated as zero for all statistical analyses.

Full details of the pharmacokinetic analysis and the corresponding statistical analysis of PK parameters will be described in the final report.

## Statistical methods

### Statistical methods for primary and secondary outcomes {20a}

This and the following sections briefly specify the statistical analysis principles for the study. Final and detailed specifications on the quantitative analyses described here will be provided correspondingly in the statistical analysis plan to be finalized prior to unblinding of the study.

The general level of significance used is *α* = 5% (two-sided). However, this will only be considered as confirmatory within the multiplicity adjusted statistical analysis of the primary endpoints and the key secondary endpoints.

#### Analysis sets

The “all enrolled set” includes all subjects enrolled into the study who have provided at least some data. The “full analysis set” consists of the subjects in the all enrolled set that have been randomized. The “safety set” includes all subjects of the full analysis set that have received at least one dose of any study medication. Further analysis populations (e.g., per protocol set) may be defined in the statistical analysis plan.

Unless otherwise specified in the respective sections below the following populations will be used for the analyses. Demographic and baseline characteristics analyses will be based on the all enrolled set and, optionally, the full analysis set or safety set. Efficacy data (primary and secondary endpoints) will be analyzed based on the full analysis set using the intent-to-treat principle, i.e., a subject will be assigned to the treatment group he or she was randomized to. Safety analyses will be based on the safety set. Should there be a huge discrepancy between some populations, such as safety set being less than 90% of all enrolled set, some analyses may additionally be conducted for the different analysis set.

#### Definition of the primary endpoints

The first primary endpoint is the percentage of change in amplitude of the negative-positive vertex potential (N2-P2 complex) of LEPs at time-point T + 60 min post-drug administration vs. the pre-drug time-point, at the non-sensitized arm. The second primary endpoint is the percentage of change in amplitude of the N2-P2 complex of PEPs at time-point T + 60 min post-drug administration vs. the pre-drug time-point, at the sensitized arm.
$$ \mathrm{endpoint}=\frac{\mathrm{N}2-\mathrm{P}{2}_{\mathrm{amp}}\left(+60\ \min \right)-\mathrm{N}2-\mathrm{P}{2}_{\mathrm{amp}}\left(\mathrm{baseline}\right)}{\mathrm{N}2-\mathrm{P}{2}_{\mathrm{amp}}\left(\mathrm{baseline}\right)} $$

The primary analysis of the two primary endpoints will focus on the comparison of the tapentadol vs. placebo effects.

Within the error-controlled testing procedure, both primary endpoints will also be tested in key secondary analyses comparing lacosamide vs. placebo and pregabalin vs. placebo effects. Also within the error-controlled testing procedure, the key secondary analyses will also compare a third endpoint: the percentage of change in amplitude of ongoing theta band EEG oscillations at time-point T + 60 min post-drug administration vs. the pre-drug time-point.
$$ \mathrm{endpoint}=\frac{{\mathrm{theta}}_{\mathrm{amp}}\left(+60\min \right)-{\mathrm{theta}}_{\mathrm{amp}}\left(\mathrm{baseline}\right)}{{\mathrm{theta}}_{\mathrm{amp}}\left(\mathrm{baseline}\right)} $$

#### Definition of secondary endpoints

The following secondary endpoints will be investigated:
The percentage of change in the intensity of the sensation elicited by laser stimulation of the non-sensitized forearm at time-point T + 60 min post-drug administration vs. the pre-drug time-point.The percentage of change in the intensity of the sensation elicited by mechanical pinprick stimulation of the sensitized forearm at time-point T + 60 min post-drug administration vs. the pre-drug time-point.
$$ \mathrm{endpoint}=\frac{{\mathrm{pain}}_{\mathrm{intensity}}\left(+60\min \right)-{\mathrm{pain}}_{\mathrm{intensity}}\left(\mathrm{baseline}\right)}{{\mathrm{pain}}_{\mathrm{intensity}}\left(\mathrm{baseline}\right)} $$

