Ongoing EEG. Two 2.5 min recording of ongoing EEG will be performed, while the participant is at rest, and not exposed to any sensory stimuli. Each recording will include 1 min of EEG recording with eyes opened, one 30-s period with eyes closed, followed by a second 1-min recording with eyes opened. A frequency analysis of the magnitude of ongoing EEG oscillations will be used to assess the amplitude of ongoing EEG oscillations within the delta (1–4 Hz), theta (4–7 Hz), alpha (8–12 Hz), beta (15–30 Hz), and gamma (40–90 Hz) oscillations, eyes opened and eyes closed. The signal processing steps are described in the operational manual. This will allow generating the key secondary endpoint “theta_amp” by averaging the amplitude of theta band oscillations across the two 1-min EEG segments eyes opened.Laser-evoked brain potentials (LEP). Brief laser heat stimuli lasting only a few milliseconds will be applied to the skin to activate selectively heat-sensitive nociceptors of the skin, as detailed in the operational manual. The thermal stimuli will be produced by a commercially available infrared neodynium:yttrium aluminum perovskite (Nd:YAP) laser stimulator designed for the recording of LEPs. Intensity of stimulation will be set to consistently activate A-delta and C fiber heat-sensitive nociceptors. The device will be used in accordance with safety guidelines, by trained and authorized personnel, as detailed in the operational manual. The Nd:YAP laser is routinely used for diagnostic purposes [34, 35]. The laser stimulator generates a radiant heat stimulus able to heat the skin above the thermal activation of heat-sensitive nociceptors in only a few milliseconds, without producing any skin lesion. The sensations produced by laser stimuli are often described as a brief pinprick, a light burn, or a diffuse warmth. They may be perceived as unpleasant. On rare occasions, the laser stimulus produces a slight punctuate erythema, which may subsequently become hyperpigmented, but always vanishes completely within a few days [36]. In each of the four LEP recording blocks (two blocks per forearm), the laser stimuli will be repeated 15 times, with a randomly varying inter-stimulus interval. The target of the laser stimulus will be slightly displaced during each inter-stimulus interval, to avoid overheating the skin and/or inducing receptor sensitization and/or habituation. After each laser stimulus, the subject will be requested to rate the intensity of the elicited sensation as detailed in the next section. After each stimulation block, the subject will be requested to rate the unpleasantness of the elicited sensation, as detailed in the next section. This EEG data will allow measuring the average amplitude of the negative-positive (N2-P2) vertex potential elicited by laser stimulation [3], required to generate the primary endpoint “LEP N2-P2_amp,” also used for the key secondary analyses. The processing steps to obtain this measurement are detailed in a separate operational manual.Pinprick-evoked brain potentials (PEP). Preferential activation of mechano-sensitive skin nociceptors will be achieved by applying calibrated mechanical pinprick stimuli using small surface probes. The device, provided by MRC Systems, is detailed in a separate operational manual. The time of contact of the needle with the skin is obtained using an internal switch which generates a trigger marking the onset of each stimulus in the ongoing EEG recording. The stimuli will be applied manually by the operator, as detailed in the operational manual. The sensation generated by pinprick stimulation is most often described as pricking. The probe does not penetrate the skin and, hence, does not produce any lesion. For each of the four PEP recording blocks (left forearm: two blocks, right forearm: two blocks), the pinprick stimuli will be repeated 15 times, with a randomly varying inter-stimulus interval. The target of the pinprick stimulus will be slightly displaced during each inter-stimulus interval, to avoid receptor sensitization and/or habituation. After each pinprick stimulus, the subject will be requested to rate the intensity of the elicited sensation. After each stimulation block, the subject will be requested to rate the unpleasantness of the elicited sensation. This EEG data will allow measuring the average amplitude of the negative-positive (N2-P2) complex elicited by pinprick stimulation [5], required to generate the primary endpoint “PEP N2-P2_amp,” also used for the key secondary analyses. The processing steps to obtain this measurement are detailed in a separate operational manual.Auditory-evoked brain potentials (AEP). In addition to exerting a selective effect on nociception, the medications as well as the procedure used to induce hyperalgesia may induce unspecific changes in brain function, such as changes in the level of vigilance (e.g., drug-induced sedation). For this reason, AEPs will be recorded as a control to assess effects that are not specific for nociception [32]. The AEPs will be elicited by short-lasting auditory stimuli presented binaurally at a comfortable listening level (see separate operational manual). Such as for PEPs and LEPs, the auditory stimuli will be repeated 15 times in each block, with a randomly varying inter-stimulus interval. Such stimuli, delivered using relatively long and variable inter-stimulus intervals, are expected to generate a late-latency negative-positive complex (N1-P2), maximal at the scalp vertex, related to brain functions that are, at least in part, similar to those underlying the LEP and PEP N2-P2 response [37]. For each recording block, the amplitude of the N1-P2 will be measured as detailed in the operational manual.

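### The two secondary pain-rating endpoints are percentage changes on a scale that starts at zero, so they are unstable and skewed upward when the pre-dose rating is low

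*Protocol article*

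**What the plan says.** All references are to the protocol article. The section that defines the secondary endpoints lists two, both at T+60 min against the pre-drug time-point: "The percentage of change in the intensity of the sensation elicited by laser stimulation of the non-sensitized forearm" and "The percentage of change in the intensity of the sensation elicited by mechanical pinprick stimulation of the sensitized forearm". One formula serves both: (rating at +60 min − baseline rating) / baseline rating.

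The section on pain intensity and unpleasantness ratings gives the scale, a "101-point pain rating scale where 0 is defined as “no pain at all". It also says that "Average pain ratings and unpleasantness ratings obtained at each PD assessment time-point" are calculated, which implies that an average enters the formula.

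The LEP description gives the number of ratings behind that average. Each forearm has two blocks, and in each of them "the laser stimuli will be repeated 15 times, with a randomly varying inter-stimulus interval". The PEP description has the same layout. The laser sensation is "often described as a brief pinprick, a light burn, or a diffuse warmth", and laser intensity is set to activate nociceptors rather than to reach a given rating.

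The section on analysis of secondary endpoints applies the primary-endpoint approach and calls the results exploratory. The eligibility tables (Tables 1 to 3) set no minimum rating, and the text gives no offset and no rule for a zero or low baseline.

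**The concern.** A percentage change behaves well only when its denominator stays well away from zero. Here the denominator is a pain rating. A healthy volunteer who feels mainly warmth from the laser can properly answer at or near zero, so a shift of a few points can become a change of several hundred percent.

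The measure is also asymmetric: it cannot fall below −100% and has no practical upper limit. The planned mixed model with compound symmetry assumes one common variance, whereas the variance of this ratio grows as the baseline falls. Each period has its own baseline, so the same subject can be unremarkable in one period and extreme in another.

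At stake is the readability of the perceptual results. The trial design section says that the ratings will be used to relate EEG changes to changes in perceived pain. A few low raters could dominate the treatment means and inflate the standard error.

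**Working it through.** The document gives no power, SD or baseline distribution for these endpoints, so there is no stated figure to reproduce.

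**1. The formula at low baselines.** Endpoint = 100 × (rating at +60 min − baseline) / baseline.

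| Baseline | +3 points | +5 points |
|---|---|---|
| 0 | undefined | undefined |
| 0.5 | +600% | +1000% |
| 1 | +300% | +500% |
| 2 | +150% | +250% |
| 5 | +60% | +100% |
| 20 | +15% | +25% |
| 40 | +7.5% | +12.5% |

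One subject going from 1 to 6 scores (6 − 1)/1 = +500%. This adds 500/12 = 41.7 percentage points to a 12-subject mean, or 500/48 = 10.4 to a 48-subject mean. Twelve is the overall evaluable number in the sample size section; 48 is four centers at the upper figure of 12.

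For the skew, take two subjects who swap values. One goes from 1 to 6 (+500%) and the other from 6 to 1 (−5/6 = −83%). The mean change in points is 0, but the mean percentage change is (500 − 83)/2 = +208%. The same swap between 40 and 45 gives (12.5 − 11.1)/2 = +0.7%.

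**2. How likely is an exact zero?** Two blocks of 15 stimuli give 30 ratings per forearm per time-point. If q is an assumed probability that a single rating is 0, independent across stimuli, then P(average = 0) = q^30. For 48 × 4 = 192 subject-periods, P(at least one) = 1 − (1 − q^30)^192.

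| q | P(average = 0) | At least one in 192 |
|---|---|---|
| 0.5 | 9 × 10⁻¹⁰ | about 2 × 10⁻⁷ |
| 0.7 | 0.002% | 0.4% |
| 0.8 | 0.1% | 21% |
| 0.9 | 4.2% | over 99.9% |

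An exact zero therefore needs a subject who rates almost every stimulus as painless. Ratings within a person are not truly independent, so a consistent non-responder is somewhat more likely than this suggests.

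**3. Cost in precision.** Simulation with 1,500 runs per scenario. Assumptions: lognormal true ratings, noise SD of 4 points on each averaged rating, a true 30% reduction, and paired t tests at two-sided 0.05. Subjects with a zero baseline are left out of the percentage analysis.

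| Median rating (log-SD) | Subjects | Power, percent change | Power, change in points |
|---|---|---|---|
| 40 (0.4) | 48 | 99.7% | 100% |
| 20 (0.8) | 48 | 61% | 99.9% |
| 10 (0.8) | 48 | 26% | 92% |
| 40 (0.4) | 12 | 96% | 99% |
| 20 (0.8) | 12 | 38% | 71% |
| 10 (0.8) | 12 | 15% | 29% |

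With 48 subjects, the median SD of the paired percentage difference rises from 22 points to 87 and then 202 across the three scenarios.

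Three cautions apply. The log-SD changes along with the median. The noise is constant and ratings are cut off at zero, which produces zero and near-zero averages more readily than 30 averaged ratings might. The comparison is a paired test on change in points, not the full mixed model with a baseline covariate.

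**The case against.** The strongest reply is that nothing shows low baselines will occur. Laser intensity is set to activate nociceptors consistently, a light burn is among the listed sensations, and 30 ratings are averaged. The pinprick endpoint is on the arm sensitized by HFS before the pre-dose assessment, where the protocol expects marked hyperalgesia. The analyses are exploratory, and the SAP, not shown here, may contain a handling rule.

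Most of this stands and limits the point. It makes the concern weaker for pinprick than for laser, and conditional on baseline ratings that are not reported. It does not remove it: the ratio is fixed in the protocol, and a rule for zero baselines would not cure instability at low non-zero ones.

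A reader might infer four stronger things that the document does not support:

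- **That the endpoint is undefined for some subjects.** It can be, but no baseline data show that it will be.
- **That exclusion would depend on outcome.** The denominator is measured before dosing in a blinded crossover, so any loss selects on pre-dose sensitivity.
- **That the least sensitive subjects would drop out of the analysis.** A zero baseline makes only that period's value undefined, and the mixed model can use the subject's other periods.
- **That these endpoints are the only perceptual check.** Unpleasantness ratings, single-stimulus ratings and hyperalgesia testing are also collected.

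**Conclusion.** The point holds in a limited form. The protocol fixes a ratio that can be undefined at a zero baseline and, more plausibly, is unstable and skewed upward at low baselines, mainly for laser on the non-sensitized forearm. The size depends on the unreported distribution of pre-dose ratings. Under the stated simulation assumptions the loss is negligible at a median near 40 and large at medians of 20 or 10. The +500% example rests on an assumed baseline of 1. The primary and key secondary tests are unaffected. The change is still worth making, because the alternative uses data already collected and lost no power to percentage change in any scenario examined.

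**What to change.** For both rating endpoints, analyse the mean rating at T+60 min in scale points, with the same period's pre-dose mean rating as covariate in the same mixed model. Report the drug-placebo differences in points with confidence intervals. Percentage change may stay as a descriptive supplement, with a stated rule for zero baselines. State explicitly that the time-point average is the value analysed.

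No new data are needed. The main cost is that the ratings will no longer share a unit with the EEG endpoints. The change needs an SAP entry before unblinding and, if the study is still ongoing, a protocol amendment, as the closing paragraph of the test-retest reliability section requires.
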